### **4.2 Inclusion criteria**

To be eligible to participate in this study, a subject must complete the screening questionnaire and meet all of the following criteria: - being eighteen years or older and meeting the diagnostic criteria for prolonged grief disorder and insomnia disorder (as specified in the DSM-5-TR).

### **4.3 Exclusion criteria**

Recently started (<3 months) or changed use of sleep medication or off-label sedating medication for insomnia complains, being diagnosed with, but not yet treated for, a different sleep disorder (particularly obstructive sleep apnea syndrome, restless legs syndrome), doing shiftwork, having traveled across time zones during the last week (>4hours time difference), being diagnosed with a schizophrenia spectrum disorder, a substance use disorder, being suicidal, or mental retardation, or being unable to adequately read or speak Dutch will lead to exclusion from the study, to ensure unbiased evaluation of treatment effects (cf. van der Zweerde et al., 2020).

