### 5.2 Use of co-intervention (if applicable)

Participants will be instructed not to seek additional psychological counselling for prolonged grief disorder during the study. They will be allowed to seek psychological care for other psychological disorders. Participants will be asked at the start of the study and after completion if they have received any additional care.

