#### **8.1.1 Main study parameter/endpoint**

The primary aim is to assess the effect of CBT-I on prolonged grief symptoms. To assess this effect, prolonged grief symptoms will be measured weekly for a period of 26 weeks starting parallel to the waiting period and continuing through the treatment phase. The mean difference in symptom levels between the baseline phase (waiting period) and treatment phase will serve as the primary outcome.

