### Measures used during the study

- The Holland Sleep Disorder Questionnaire (HSDQ; Kerkhof et al., 2013) is a validated, Dutch, self-assessment questionnaire to screen for sleep disorders, such as insomnia disorder, sleep-related breathing disorders, and sleep-related movement disorders.
- The Traumatic Grief Inventory Plus (TGI-SR+; Lenferink et al., 2022) is a validated questionnaire that assesses all current symptoms of disturbed grief, including PGD as per ICD-11 and DSM5-TR. We will use the 12 items reflecting symptoms of DSM-5-TR PGD. We will use the original version, assessing symptoms over the past month, as well as an adapted version assessing symptoms over the past week.
- The Traumatic Grief Inventory Clinician Administered (TGI-CA; Lenferink et al., 2023) is an interview to assess all current criteria for disturbed grief, including PGD per ICD-11 and DSM-5-TR. We will use the 12 items reflecting symptoms of DSM-5-TR PGD.
- The Structured Clinical Interview for DSM5 Sleep Disorders Revised (SCISD-R; Taylor et al., 2018) is a well-validated clinical interview to assess DSM-5-TR sleep disorders, including insomnia disorder.

- The Insomnia Severity Index (ISI; Bastien et al., 2001) is a widely used and validated questionnaire that assesses insomnia severity. Items cover both day- and nighttime symptoms as well as worries about sleep. The ISI will be slightly adjusted to assess symptoms in the last week.

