Second, we will use Tau-U to quantitatively assess the differences between the baseline and intervention phase at an individual level. Tau-U is a non-overlap index (between the phases) that corrects for possible trends in the data (Parker et al., 2011). Hereafter, a randomization test will be used to assess the overall effect of the intervention. The randomization test is based on the random assignment of baseline length (i.e., moment of phase change; (Michiels & Onghena, 2019). This non-parametric test compares the mean difference of all possible baselines (10 per person in the current study) with the mean difference between the actual baseline and treatment phase. The place in the rank order of the mean differences determines the p-value of the test. The null hypothesis is that there is no difference between the baseline and treatment phases. The alternative hypothesis is that there is a difference between the two phases. To check for the potential effects of receiving treatment through telehealth versus face-to-face treatment, we will also run the randomization tests for the two treatment options separately.

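### Section 4.3 admits people who have only just started treatment for another sleep disorder, although the same sentence sets a three-month start-or-change window for insomnia medication

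*Protocol*

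**What the plan says.** Protocol section 4.3 puts its exclusions in one sentence and gives their purpose: "to ensure unbiased evaluation of treatment effects". Two of them concern sleep treatment.

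- Medication: "Recently started (<3 months) or changed use of sleep medication or off-label sedating medication for insomnia complains". This carries a time window and covers both starts and changes.
- Other sleep disorders: "being diagnosed with, but not yet treated for, a different sleep disorder (particularly obstructive sleep apnea syndrome, restless legs syndrome"). This carries no time window, no stability condition and no requirement that treatment is ongoing.

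Three other parts of the protocol bear on the point.

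- Section 8.3 uses the HSDQ, a "self-assessment questionnaire to screen for sleep disorders, such as insomnia disorder, sleep-related breathing disorders, and sleep-related movement disorders", and a structured sleep-disorder interview. It gives entry cut-offs for the ISI and the TGI-SR+ but none for the HSDQ.
- Section 5.2 limits one kind of co-intervention: "Participants will be instructed not to seek additional psychological counselling for prolonged grief disorder during the study". It adds: "Participants will be asked at the start of the study and after completion if they have received any additional care". The answer has no stated role in eligibility.
- Section 8.1.1 defines the outcome: "The mean difference in symptom levels between the baseline phase (waiting period) and treatment phase will serve as the primary outcome". Section 10.1 adds plots for each participant, Tau-U for each participant and an overall randomization test.

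**The concern.** The medication rule shows that the sponsor regards a recent change in sleep treatment as a threat to the evaluation. The sleep-disorder rule names apnea and restless legs as particular concerns, yet depends only on whether treatment has begun. A person can meet insomnia criteria at the interview, have started treatment for apnea the week before, and pass.

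If that treatment works gradually, symptoms fall over the 26 weekly measurements whatever CBT-I does. Later weeks are always treatment-phase weeks, so the treatment-phase mean lies below the baseline mean. The ISI would be affected directly. The TGI-SR+ would be affected only through the insomnia-to-grief link that the trial sets out to test. Section 3 presents the reading of individual patients as an advantage of the design, so an artefact in one person matters even when the group result barely moves.

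**Working it through.** The protocol gives no figure for this point, so there is none to reproduce. The size is shown for one participant with no CBT-I effect.

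**Inputs from the protocol:** 26 weekly measurements; baseline length b of 5 to 14 weeks, randomised (section 8.2); 20 participants; planning effect d = 1.0 (section 4.4).

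**Assumptions:** the other treatment starts at entry and lowers the score by A = 1 or 2 within-person SD in total, with time constant τ = 4 or 8 weeks; lag-1 autocorrelation 0.3.

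**1. Raw difference for the individual.** With y(t) = A·exp(-t/τ), t = 0 to 25, the difference is the mean of y from t = b onward minus the mean of y before t = b. For A = 1, τ = 4, b = 5: 0.061 - 0.645 = -0.58.

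| A | τ | b = 5 | b = 14 | mean over b = 5 to 14 |
|---|---|---|---|---|
| 1 | 4 | -0.58 | -0.30 | -0.42 |
| 1 | 8 | -0.59 | -0.41 | -0.49 |
| 2 | 4 | -1.17 | -0.60 | -0.84 |
| 2 | 8 | -1.18 | -0.81 | -0.98 |

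**2. If treatment began s weeks before entry.** The remaining drop is multiplied by exp(-s/τ).

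- s = 4: 37% (τ = 4) or 61% (τ = 8) remains.
- s = 8: 14% or 37% remains. For A = 1 the difference is then -0.04 to -0.08 SD (τ = 4) or -0.15 to -0.22 SD (τ = 8).

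**3. Tau-U.** The baseline-corrected form is (S_AB - S_A)/(n_A·n_B), where S_AB counts falls and rises between phases and S_A those within baseline. Its simulated average at b = 5, 9 and 14 is about -0.06 to -0.31 for A = 1 and -0.12 to -0.56 for A = 2. Without the other treatment it is about 0. The correction does little at b = 5 (A = 1, τ = 4: -0.31 uncorrected, -0.30 corrected) and much more at b = 14 (-0.16 to -0.06).

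**4. Group mean difference.** Divide the last column of the table by 20.

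- One participant: 0.42/20 = 0.02 to 0.98/20 = 0.05 SD.
- Three participants: 0.06 to 0.15 SD.

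The number of such participants is not in the protocol; 0 to 3 is assumed.

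**5. Overall randomization test.** The planned test was simulated with no CBT-I effect, N = 20, autocorrelation 0.3, and 0, 1, 2 or 4 participants improving from a treatment begun at enrolment (drop 1 or 2 SD, τ = 2, 4 or 8). It rejected in about 4 to 6% of trials in every setting, the same as with no such participants. The reason is that a decline already under way at entry does not depend on the randomised start week.

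**The case against.** The strongest reply is that the design was chosen for this situation. Section 3 says that varied baseline lengths separate the intervention effect from pre-existing trends, and step 5 bears this out for the one inferential test. A reader might infer that improvement from the other treatment would make the trial declare CBT-I effective. The documents do not support that reading.

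The individual readings also have some protection. Section 10.1 inspects the slope in each phase, and a fall that is steepest during baseline is a pattern that inspection could flag. It also states: "Tau-U is a non-overlap index (between the phases) that corrects for possible trends in the data". Step 3 shows that this protection is real but incomplete, and weakest for short baselines.

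The inputs lean towards the worst case. Treatment begun some weeks earlier leaves much less improvement to come. The 1 to 2 SD drop is applied without attenuation, although another sleep treatment would reach the TGI-SR+ only indirectly. The start-of-study question in section 5.2, the HSDQ and the sleep interview could bring recent treatment to light, but no eligibility rule acts on it. A statistical analysis plan, not shown here, could deal with it in the analysis but could not change who is enrolled.

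The criterion can also be read loosely, as requiring that the disorder has been adequately treated. If that is the intention, the wording should say so.

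A reader might also infer that someone who tried treatment and stopped would produce a spurious CBT-I effect. The wording does let that person in, but nothing about a treatment that has ended makes symptoms start to improve at entry. That is a secondary wording point only.

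**Conclusion.** The gap is real and narrow. Section 4.3 has no condition of current, stable treatment for another sleep disorder, although its own standard for insomnia medication has a start-or-change window. What can be biased is the raw phase-mean difference, the individual plots and, in part, Tau-U. The type I error of the overall test is not affected, and no sample-size figure changes.

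For one affected person the raw difference is about -0.3 to -1.2 SD if treatment starts at entry, falling quickly with earlier starts. The upper end is of the same order as the planning effect of 1.0, although section 4.4 does not say by which SD that effect is standardised. For the group the shift is about 0.02 to 0.05 SD per such participant at most. All of this rests on an assumed size and speed of improvement and on an unknown number of such participants, which may be zero. It is a low-severity point, worth fixing because the fix is cheap.

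**What to change.** Reword the criterion in section 4.3 to exclude people diagnosed with a different sleep disorder unless it is currently treated and that treatment was not started or changed in the last three months. This reuses the window already in the sentence. Referring to current treatment also settles the case of someone who has stopped. Ask for the start or last-change date at the eligibility interview, and allow people who fail only on the window to be re-screened.

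At 13 weeks the remaining improvement is exp(-13/4) = 4% or exp(-13/8) = 20% of the total, so the largest individual figure, -1.18 SD, falls to about -0.23 SD.

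The cost is one line, one question, and a slightly smaller pool or a delay of up to three months for the few people affected. Section 4.1 estimates 35,000 to 67,000 qualifying people a year for 20 places, so recruitment should hardly suffer.

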#### 4.4 Sample size calculation

Based on a prior small pilot study on CBT-I effects on prolonged grief symptoms (Sveen et al., 2021) and studies on CBT-I effects on depression symptoms (e.g., Christensen et al., 2016; van der Zweerde et al., 2020), we estimate a large effect size (*Cohen's d* = 1.0) on prolonged grief and insomnia symptoms. An a priori power analysis was conducted using the single case designs shiny web-app for power calculations (Bouwmeester & Jongerling, 2020). Based on power of .80, a total of 26 measurements per participant, of which minimally five during baseline phase, followed by minimally 12 measurements during the treatment (and continued monitoring) phase and an alpha of .05, sample size of 19 is required (see Table 1 for an overview). A total of 20 patients will be enrolled to ensure sufficient power. CBT-I provided generally elicits a low dropout rate (e.g., Lancee et al., 2016), in case a participant drops out, they will be replaced by another participant.

## 5. TREATMENT OF SUBJECTS

### 5.1 Investigational product/treatment

CBT-I will be delivered by a psychologist in training to become a healthcare psychologist, supervised by a registered healthcare psychologist. CBT-I consists of 6-7 weekly individual, face-to-face sessions of 1-2 hours according to the Dutch CBT-I protocol (Verbeek & van de Laar, 2023). Depending on the location of the participant, these sessions can be held either at the Heymans Institute or online using a video conference program. At four weeks post-treatment, a booster session will be planned to evaluate sleep health and, if necessary, repeat certain treatment components.

Components of CBT-I are:

*Psycho-education*: providing information about the function and regulation of normal sleep and the consequences of disturbed sleep.

*Sleep hygiene*: giving information on healthy lifestyle that can improve sleep and on behaviors that disrupt sleep.

*Stimulus control*: strengthening the associations between bed (and bedroom) and sleep by only going to bed when sleepy and leaving the bed when awake for longer than 30 min, and getting up at a fixed time and refraining from any activity other than sleep and sex in the bedroom. For mobility-impaired participants, getting out of bed during nighttime might increase the risk of falling. These participants are therefore not instructed to get out of bed. These participants will be instructed to remain in bed, and do something none sleep related and relaxing such as listening to a podcast, or reading a magazine, in low light conditions.

*Sleep restriction therapy*: restricting bedtime to the average subjective total sleep duration during the past week ( $\geq 5$  hours) and thereby elevating sleep pressure, which will result in a higher relative percentage of time slept while in bed (sleep efficiency). Based on reported sleep efficiency during the past week and participant age, bedtimes will be extended or reduced.

*Relaxation therapy*: employing various relaxation techniques to teach a person to unwind.

*Cognitive therapy*: identifying and challenging misconceptions and worries about sleep that keep a person awake.

### 5.2 Use of co-intervention (if applicable)

Participants will be instructed not to seek additional psychological counselling for prolonged grief disorder during the study. They will be allowed to seek psychological care for other psychological disorders. Participants will be asked at the start of the study and after completion if they have received any additional care.

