These side effects are similar to what is normally observed in insomnia patients. Therefore, for reasons of safety, participants are instructed to spend a minimum of 5 hours in bed each night and to refrain from driving a car or operating heavy machinery if they feel excessively sleepy during the early stages of sleep restriction therapy. Importantly, sleep restriction is a potent intervention technique that may lead to some side effects at first, but also leads to an amelioration of such experiences over time.

Additionally, minimal risks/burden are associated with the repeated measurement of symptoms of prolonged grief disorder and insomnia. This repeated measurement might elicit some negative feelings in participants. However, it is our experience from prior survey research among hundreds of bereaved adults, that they generally find it comforting to know that their grief can contribute to something positive, such as scientific knowledge. Nevertheless, to further reduce the risk of eliciting negative feelings, we will only use validated questionnaires applied successfully before in the bereaved population.

Finally, participants who still experience severe and disabling grief reactions (TGI-SR + score  $\geq 33$ , on the DSM5-TR items) at the 3-month follow-up will be offered the possibility of receiving CBT for prolonged grief disorder from a psychologist within the research team. CBT for prolonged grief disorder is the golden standard treatment for prolonged grief disorder and can be effectively delivered in person and online (e.g., Komischke-Konnerup et al., 2024; Wagner et al., 2020).

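### Current or recently started psychological treatment for prolonged grief or insomnia is not excluded at entry, and can bias the primary mean difference, though not, in general, the randomization test

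*Protocol*

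**What the plan says.** **Entry.** The inclusion criteria in protocol section 4.2 are completion of the screener and "being eighteen years or older and meeting the diagnostic criteria for prolonged grief disorder and insomnia disorder". Section 4.3 excludes "Recently started (<3 months) or changed use of sleep medication or off-label sedating medication for insomnia complains". It also lists untreated other sleep disorders, shift work, recent travel across time zones, "being diagnosed with a schizophrenia spectrum disorder, a substance use disorder, being suicidal, or mental retardation" and inadequate Dutch. Its stated purpose is an unbiased evaluation of treatment effects. No psychological treatment is named, whether for grief or for insomnia.

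**During the study.** Section 5.2 makes three statements on other care. For grief it gives an instruction: "Participants will be instructed not to seek additional psychological counselling for prolonged grief disorder during the study". For everything else the rule is permissive: "They will be allowed to seek psychological care for other psychological disorders". As to recording, the protocol has outside care queried twice, once at entry and once when the study is over, and mentions no dates.

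**Outcome and analysis.** Section 8.1.1 states: "The mean difference in symptom levels between the baseline phase (waiting period) and treatment phase will serve as the primary outcome". Section 10.1 adds visual inspection of level, trend and latency for each participant, Tau-U for each participant, and an overall randomization test over the 10 possible baseline lengths. Section 10.2 applies the same analysis to insomnia.

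**The protocol's own view of grief therapy.** The burden-and-risk part of the Summary says that "CBT for prolonged grief disorder is the golden standard treatment for prolonged grief disorder".

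**The concern.** Section 4.3 guards against a recent change in medication aimed at the secondary outcome, but has no matching guard for recently started psychological treatment aimed at the primary outcome. Someone who began grief therapy a month before screening, and still meets both diagnoses, is eligible. Section 5.2 tells that person not to seek *additional* grief counselling. It does not say what happens to the therapy already running.

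The permission in 5.2 to seek care for other psychological disorders is also loosely worded. Insomnia disorder is a disorder other than prolonged grief, so a literal reading allows outside psychological treatment of the second study diagnosis, including during a wait of 5 to 14 weeks.

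The protocol itself regards grief-focused CBT as effective. If it runs through the 26 weeks, part of the fall in grief between phases belongs to it and not to CBT-I. Section 3 gives evaluation of individual patients as a reason for choosing this design, so the participant-level readings matter as well as the group result.

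**Working it through.** **Inputs from the protocol.** 26 weekly measurements; baseline length b from 5 to 14 weeks, hence 10 possible values; 20 participants; outcome = treatment-phase mean minus baseline mean. The protocol gives no figure for the effect or frequency of other care, so there is none to reproduce.

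**Assumptions (not in the protocol).** Concurrent therapy lowers the TGI-SR+ by s = 0.2 to 0.5 points per week throughout; 3 of 20 participants are affected; CBT-I has no effect.

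**1. Mean difference.** The baseline covers weeks 1 to b, with midpoint (b + 1)/2. The treatment phase covers weeks b + 1 to 26, with midpoint (b + 27)/2. The gap is (b + 27)/2 − (b + 1)/2 = 13 weeks for every b. A steady decline therefore adds 13 × s to the apparent fall:
- s = 0.2: 13 × 0.2 = 2.6 points
- s = 0.5: 13 × 0.5 = 6.5 points

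On the group mean with 3 of 20 affected: 2.6 × 3/20 = 0.39 and 6.5 × 3/20 = 0.98, or about 0.4 to 1.0 points.

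**2. Randomization test.** The 13-week gap does not depend on b, so a steady decline adds the same constant to the difference at each of the 10 possible baselines. The rank of the observed value, and so the p-value, is unchanged. Simulation with 20 participants, no CBT-I effect and an assumed co-treatment gain of 1 within-person SD over the series covered linear, exponential and randomly timed step courses:

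| Share co-treated | Bias in mean difference (SD) | Rejection rate at alpha 0.05 |
|---|---|---|
| 10% | −0.05 to −0.06 | 0.045 to 0.060 |
| 25% | −0.12 to −0.13 | 0.046 to 0.057 |
| 50% | −0.24 to −0.26 | 0.043 to 0.053 |
| 100% | −0.48 to −0.52 | 0.051 to 0.067 |

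The 0.067 was Monte Carlo noise: the same setting (exponential, 100%) with 10,000 replicates gave 0.049. The estimate is biased and the test keeps its level.

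**3. Tau-U.** Take the usual baseline-trend-corrected form, (S_AB − S_A)/(nA × nB), where S_AB compares the phases and S_A is the trend within baseline. Under a noise-free decline with no CBT-I effect, S_AB = −nA × nB and S_A = −nA(nA − 1)/2, so Tau-U = −1 + (nA − 1)/(2nB):
- b = 5, nB = 21: −1 + 4/42 = −0.90
- b = 10, nB = 16: −1 + 9/32 = −0.72
- b = 14, nB = 12: −1 + 13/24 = −0.46

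Full correction would give 0. With an assumed weekly noise SD of 3 to 5 points and the same slopes, the average at these three baselines runs from about −0.2 to −0.76. The correction is partial, and in the noise-free case it is weakest for short baselines.

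**4. Visual inspection.** The comparison of phase means carries the 13 × s shift in full. The trend inspection offers some protection, because a decline already present in baseline can be seen.

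**The case against.** The strongest reply is that the design anticipates this. Section 3 randomises baseline length in order to separate pre-existing trends from the intervention. Therapy under way at entry cannot depend on a later random draw, so the overall test is sound. **This stands.** A reader might infer that other treatment would be credited to CBT-I by the trial's inferential result; the documents do not support that. The test is at risk only if the timing of other care depends on the assigned wait, for example if long waiters seek help elsewhere. For grief counselling, section 5.2 instructs against that. For insomnia care, on a literal reading, it does not.

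Other replies:
- *Section 10.1 looks at trends and Tau-U corrects for them.* Half right. The trend inspection helps, but Tau-U removes only part of a steady decline, as shown above. A valid p-value also does not correct a biased estimate.
- *Treatment of insomnia is not uncontrolled.* Correct for medication that was recently started or changed. It would be wrong to say that nothing excludes people already treated for insomnia. The gap is psychological treatment, and it bears on the insomnia outcome directly.
- *Additional may mean any care outside the trial.* Possible, since the last sentence of 5.2 seems to use it that way. Even so, an instruction not to seek care does not address care already being received.
- *The use made of the care questions belongs in an analysis plan.* Accepted. A SAP may exist and is not shown, so the lack of a stated use is not criticised. The entry rule, however, cannot be repaired in a SAP once people are enrolled.
- *The magnitudes are assumed.* They are, and the group shift is modest.

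**Conclusion.** The point holds in a limited form. Sections 4.2, 4.3 and 5.2 together leave ongoing or recently started psychological treatment for prolonged grief or insomnia unaddressed at entry, and leave outside psychological insomnia care permitted on a literal reading. The quantity named as primary outcome in 8.1.1 takes in the whole effect of such care; the visual comparison of phase means does the same, and Tau-U does so in part. The randomization test keeps its level of about 5% as long as the care does not follow the assigned wait.

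The size cannot be fixed from the protocol. The 2.6 to 6.5 points per affected participant and 0.4 to 1.0 points on the group mean rest on an assumed steady decline of 0.2 to 0.5 points per week and on 3 of 20 being affected. The individual readings are more exposed than the group result. This is an inexpensive improvement to make before enrolment, not a flaw that invalidates the trial.

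**What to change.** 1. **Section 4.3.** Extend the existing criterion on recently started (under three months) or changed sleep medication to cover recently started or changed psychological treatment for prolonged grief disorder or insomnia disorder, and check it at entry. This follows the section's stated aim and keeps its treatment of stable use.
2. **Section 5.2.** The sponsor should reconcile it with 4.3 on two matters: what applies to grief care already under way, and whether psychological care for insomnia falls under the permission for other disorders. Deleting the word *additional* would not settle the first, because the sentence would still speak only of seeking care. Which rule is clinically right is for the sponsor to decide.
3. **Data collection.** When asking about other care at the start and after completion, record its type and its start and stop dates. The mean difference and Tau-U can then also be reported without affected participants, as a supplement to the intention-to-treat analysis of section 10. The dates also show whether care began during long waits, the one route by which the test could be affected.

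**Cost.** A protocol amendment with one added criterion and a clarified paragraph, a few more fields on a questionnaire, and one small sensitivity analysis. A few applicants will be lost, which should be tolerable for a target of 20 given the 35,000 to 67,000 people per year that section 4.1 estimates would qualify. Long-standing stable therapy would still be admitted, which is why the dates are needed as well.
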